**Primary outcome measures**							
**Adherence**							
Clinic-based adherence to physiotherapist’s recommendations			#	#	#	#	
General adherence to physiotherapist‘s recommendations				✓	✓	✓	✓
Specific adherence to back exercises and physical activity advice				✓	✓	✓	✓

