### Sample size

The sample for the study was calculated using data from our recent pilot study [36]. The effect sizes observed in that investigation were *d* = .4 for adherence and satisfaction with back pain, and *d* = .5 for PA-walking behavior. These effect sizes are similar to those reported in a recent Cochrane review of trials investigating the effectiveness of interventions designed to increase adherence among chronic pain patients [16]. As a result, the estimated sample required for 80% power (α = .05) to detect a between arm effect of d = .4 in a non-clustered RCT, using a t-test, would be 156 (*n* = 78 per arm).

To account for the clustered nature of the data, we multiplied this sample size by a correction factor of 1 + (*m* − 1)ρ, where *m* was the mean expected cluster size and ρ was the anticipated intracluster correlation coefficient [38]. Based on previous research in clinical settings regarding physical activity in patients with CLBP [18,23], we estimated that the ICC would be 0.03. Assuming we recruit *m* of 22 patients per clinic, the correction factor is 1.63 for our cluster-randomized design. To account for the clustered design, the study would require 254 participants to achieve 80% power for the adherence and LBP related data.

We anticipate that approximately 15% of participants will not complete follow-up assessments [39]. Traditionally, one would account for this loss to follow up and increase the sample size by 15% to 292 participants (146 per arm). However, as our method of analysis (linear mixed models, see statistical methods section) does not require list-wise deletion, and therefore loss to follow-up is expected to have negligible impact. Indeed, Chakraborty and Gu [40] demonstrated that up to 20% of the observations can be missing without a meaningful loss of power for mixed modeling approaches. As such, our intended sample of 292 patients will provide more than 80% power to detect significant effects in these primary outcomes.

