### Statistical methods

Researchers will analyze the data using a coded dataset and these individuals will not become unblinded until analysis is complete. Participants’ data will be analyzed according to their assigned arm of the study, regardless of whether they attend their physiotherapy treatment sessions or not (i.e., intention-to-treat principle).

Fidelity of the intervention will be assessed in a subsample of patients. We will employ between-arm comparisons of autonomy support ratings made by (i) patients, (ii) physiotherapists and (iii) independent, blinded raters of audio recordings. We will also compare 5A strategy use, as measured by independent, blinded raters of audio recordings.

The main study hypotheses will be explored using linear-mixed modeling with measurement occasions, patients, physiotherapists, and clinics as potential levels of the analysis. Using a dummy-coded “treatment” variable (experimental vs. control) as a predictor in the model, we will test differences both in the mean levels and the rates of change of the primary and secondary outcome variables. The primary endpoint for the analysis will be data collected at week 24. Lastly, in order to examine the process of change, we will conduct a structural equation modeling analysis, accounting for clustering effects, to test the direct and mediated relationships outlined in Figure 2.

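### Avoiding list-wise deletion does not make loss to follow-up negligible for week-24 patient-rated adherence, and about 80% power, not more, is what the expected loss leaves

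*Protocol article*

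**What the plan says.** The Sample size section sets the unclustered requirement from "80% power (α = .05) to detect a between arm effect of d = .4 in a non-clustered RCT, using a t-test", which it says "would be 156 (*n* = 78 per arm"). For clustering, "we estimated that the ICC would be 0.03", and "Assuming we recruit *m* of 22 patients per clinic, the correction factor is 1.63"; this takes the requirement to 254.

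On loss it says: "We anticipate that approximately 15% of participants will not complete follow-up assessments". It describes 292 as the traditional inflation by 15%, then argues that the allowance is hardly needed, because the planned analysis "does not require list-wise deletion, and therefore loss to follow-up is expected to have negligible impact". It adds a citation that up to 20% of observations can be missing from a mixed model without meaningful loss of power. It concludes that 292 patients give more than 80% power for these primary outcomes.

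Under Statistical methods: "The primary endpoint for the analysis will be data collected at week 24".

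In Table 3, the row "General adherence to physiotherapist‘s recommendations" and the row for specific adherence to exercises and activity advice are ticked at weeks 1, 4, 12 and 24 only. Clinic-based adherence is rated by the physiotherapist after each session, from the first session on, with no mark at week 24. Self-reported activity, pain, bothersomeness, function and quality of life all have a pre-treatment tick.

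**The concern.** A mixed model keeps every patient who has at least one observation of the outcome. That limits the damage from loss to the extent that lost patients have other observations of the same outcome, and that those observations predict the missing value. For outcomes with a pre-treatment score, every enrolled patient has one. For patient-rated adherence, one of the outcomes the trial was sized on, a patient who never responds after enrolment has none. Avoiding list-wise deletion cannot help with that patient.

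The conclusion is also broader than its support. As the article reports it, the cited result concerns power. It says nothing on whether the week-24 contrast stays unbiased when loss depends on values that were not observed.

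Two things are at stake: the stated margin above 80% power, which treats the 15% allowance as surplus, and a reassurance about loss that a reader could carry over from power to bias.

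**Working it through.** **Inputs, all from the protocol article.** Sample size: d = 0.4, 80% power, α = 0.05 with sidedness not stated, 156 unclustered, ICC 0.03, m = 22, factor 1.63, 254 after clustering, 15% loss, 292 recruited. Centers: 12. Table 3: timing of the adherence measures.

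**1. Reproducing the plan's figures.**
- Unclustered, two-sample t-test at d = 0.4: one-sided α = 0.05 gives 77.97 per arm, i.e. 78 and 156 in total. Two-sided gives 99 (normal approximation) to 100 (t) per arm. So 156 matches only a one-sided test.
- Design effect: 1 + (22 − 1)(0.03) = 1.63; 156 × 1.63 = 254.3, i.e. 254.
- Inflation: 254 × 1.15 = 292.1, i.e. 292.

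**2. The inflation.** If 15% give no week-24 adherence information, 292 × 0.85 = 248.2 remain, 5.8 below 254. To keep 254 after 15% loss takes 254/0.85 = 298.8, i.e. 299.

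**3. Power with and without the loss.** Mean cluster size m = N/12, design effect 1 + (m − 1)(0.03), effective N = N/design effect, noncentral t at d = 0.4, one-sided 0.05 as reproduced in step 1:

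| Patients informative | m | Design effect | Effective N | Power |
|---|---|---|---|---|
| 292 | 24.33 | 1.70 | 171.8 | 83.3% |
| 248.2 | 20.68 | 1.59 | 156.1 | 80.0% |
| 248.2, factor held at 1.63 | – | 1.63 | 152.3 | 79.2% |

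The loss costs 3 to 4 percentage points.

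**4. If every lost patient has an earlier adherence score.** Let f = 0.15 be the fraction missing at week 24, and r the correlation of the earlier score with week 24 (an assumption; the article gives none). The variance of the week-24 mean is inflated by 1 + [f/(1 − f)](1 − r²), with f/(1 − f) = 0.1765:
- r = 0.3: 1 + 0.1765 × 0.91 = 1.161; 292/1.161 = 252; power 80.3%
- r = 0.5: 1 + 0.1765 × 0.75 = 1.132; 292/1.132 = 258; power 80.8%
- r = 0.7: 1 + 0.1765 × 0.51 = 1.090; 292/1.090 = 268; power 81.6%

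Earlier scores recover part of the loss, not all of it. The article does not split the 15% into never-responders and later dropouts, so the answer lies between steps 3 and 4.

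**5. Bias, as illustration only.** If non-responders score g SD below responders, a comparison of responders shifts by g × (difference in loss between arms). With 15% loss in both arms the shift is 0. With 10% versus 20% and g = 0.25 to 0.75, it is 0.025 to 0.075 SD, against a target of 0.4 SD. Both g and the unequal loss are assumptions. A mixed model would remove the part explained by earlier observed scores.

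**The case against.** The other side has a good deal right.

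- *Most lost patients may still contribute.* Adherence is asked from week 1, so only patients lost before week 1 leave no patient-rated score. A reader might infer that any patient lost to follow-up adds nothing; Table 3 does not support that. This stands.
- *Adherence is not the only sizing outcome.* The section also sizes on satisfaction with back pain, which Appendix A places in the bothersomeness set; that set has a pre-treatment value. The point therefore concerns patient-rated adherence and does not extend to the outcomes with a baseline score. This stands.
- *248 is not really short.* The 254 assumes 22 per center. With smaller clusters, solving N = 156[1 + (N/12 − 1)(0.03)] gives N = 248.07, which 248.2 just meets. This stands as to power: it is why 248 gives 80.0%. It does not rescue the margin above 80%, nor the article's own statement that 254 are required.
- *The sentence is about power, and 292 is still recruited.* True, and so the consequence is small. But the wording is wider than power, and the closing claim counts the allowance as extra power when the expected loss uses most or all of it.
- *Bias is conjecture.* A reader might infer that non-responders are the worse adherers and that the week-24 contrast is therefore biased. The article neither says nor quantifies this, loss explained by earlier observed adherence is handled by the model, and equal loss gives no shift in the illustration. Nor does the sentence discourage attention to withdrawal: the follow-up and data integrity sections describe active retention and recovery of missing data.
- *A sensitivity analysis belongs in the analysis plan.* Agreed. Its absence from the article is no finding.

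**Conclusion.** The point holds in limited form. Avoiding list-wise deletion does not by itself make loss negligible for week-24 patient-rated adherence, because that outcome has no pre-treatment value and the cited support concerns power only. On the protocol's own basis, the expected loss brings power from 83% to about 80% (79% with the factor fixed at 1.63), or to about 80–82% if all lost patients have an earlier score. The stated margin above 80% is therefore largely or wholly used up, but the design is not left badly underpowered by loss.

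These figures rest on the one-sided 0.05 test that alone reproduces 156, ICC 0.03, 12 equal centers, and assumed correlations of 0.3 to 0.7. With a two-sided test the same comparison is 74.1% with 292 and 69.9% with 248. That gap comes from the sidedness of the base figure, not from loss, and is the larger matter. Bias from loss remains a possibility under stated assumptions.

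**What to change.** In the Sample size section:

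1. Delete the negligible-impact sentence, or limit it to power and to patients with at least one score for the outcome concerned.
2. State that about 248 of the 292 patients are expected to give week-24 adherence data, and restate power as about 80% on that number, with the sidedness of the test given. If the test is two-sided, the figure must be recalculated on that basis.
3. State that the mixed model relies on data being missing at random given the observed scores.

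Optionally, the analysis plan can pre-set one sensitivity analysis for week-24 adherence that shifts the imputed values of non-responders downward, in each arm separately. If the physiotherapists' session records are used as imputation predictors, imputation should be done within arm, because those ratings come from unblinded physiotherapists on forms that differ between arms.

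The cost is a few sentences, a slightly less favorable power statement and, if the option is taken, one analysis on data already collected. On the protocol's own one-sided basis, no additional patients or visits are needed.

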### Statistical methods

Researchers will analyze the data using a coded dataset and these individuals will not become unblinded until analysis is complete. Participants’ data will be analyzed according to their assigned arm of the study, regardless of whether they attend their physiotherapy treatment sessions or not (i.e., intention-to-treat principle).

Fidelity of the intervention will be assessed in a subsample of patients. We will employ between-arm comparisons of autonomy support ratings made by (i) patients, (ii) physiotherapists and (iii) independent, blinded raters of audio recordings. We will also compare 5A strategy use, as measured by independent, blinded raters of audio recordings.

The main study hypotheses will be explored using linear-mixed modeling with measurement occasions, patients, physiotherapists, and clinics as potential levels of the analysis. Using a dummy-coded “treatment” variable (experimental vs. control) as a predictor in the model, we will test differences both in the mean levels and the rates of change of the primary and secondary outcome variables. The primary endpoint for the analysis will be data collected at week 24. Lastly, in order to examine the process of change, we will conduct a structural equation modeling analysis, accounting for clustering effects, to test the direct and mediated relationships outlined in Figure 2.

### Adverse events

No adverse events are expected as a result of communication skills training. Patients and physiotherapists will be informed that any adverse events should be reported to and will be documented by the research team.

## Discussion points

### Potential inconveniences to the participant

As part of the study, participants will be asked to volunteer their time for the following activities that are beyond the requirements of a normal physiotherapy session; (i) baseline assessment which will require approximately 20 minutes before their initial physiotherapy appointment and five minutes after the session to complete the assessment booklet; (ii) during weeks 1, 4, 12, and 24 all participants are asked to wear a pedometer during waking hours and (iii) during week 1, five minutes will be needed to complete follow-up assessments (iv) during week 4, 12, and 24, approximately 15 minutes will be required to complete follow-up assessments.

### Limitations

Pedometers are limited as tools to measure physical activity. For example, they only provide a total number of steps in a given period, so they cannot measure the intensity of PA at a given time point or the proportion of time spent in activity above a certain intensity during a particular period. However, limited funding for this project means that it will not be possible to include more costly measures, such as accelerometers, that would likely provide more detailed data regarding physical activity.

In line with SDT tenets, the communication skills training intervention in this trial was designed to teach physiotherapists strategies that would support patients’ basic psychological needs for autonomy, competence, and relatedness. While the health behavior change model [30], upon which our study hypotheses are largely based, does not specifically include autonomy or relatedness perceptions, these constructs are theoretical mediators (along with competence) of the relationship between autonomy support and autonomous motivation [27]. As such, it would have been preferable to measure perceptions of autonomy and relatedness. Unfortunately, to the authors’ knowledge, there are no existing measures designed to tap these constructs in the physiotherapy setting or in the context of CLBP rehabilitation. We attempted to adapt measures of autonomy and relatedness from a similar context [41], but pilot data indicated significant difficulties in operationalizing these constructs. Thus, we decided not to include these measures. Further research is needed to develop scales to measures these constructs in the CLBP patient population.

## Appendix A

### General information

****·*******Demographic Information:*** Each participant will have a consultation with the Research Physiotherapist to collect demographic information and medical history. (i.e. age, gender, education level, occupation and work status, past medical history, and low back pain history).

### Primary outcomes

#### Adherence

**·****Sports Injury Rehabilitation Adherence Scale:** This questionnaire is designed to measure physiotherapists’ perceptions of their patient’s rehabilitation adherence. It has been shown to be a reliable scale for use in clinical physiotherapy [42].

**·****Adherence to Physiotherapist’s Recommendations Scale:** To measure overall levels of adherence, we will employ the two-item adherence scale previously employed by Chan et al. [26]. The scale demonstrated acceptable internal consistency in their study involving physiotherapists.

**·****Home Exercise Compliance Assessment**: To measure specific adherence to back exercise and physical activity advice we will calculate the percentage of prescribed sessions completed per week (Note: # prescribed session per week will be self-reported and confirmed from physiotherapists’ records). This measure has been previously employed in LBP studies [10].

#### Physical activity (PA)

**·****International Short Form Physical Activity Questionnaire (IPAQ):** This questionnaire has produced reliable and valid scores across diverse populations [43].

#### Back pain symptoms

**·****Pain Intensity Numerical Rating Scale (Pain NRS)**: The pain intensity NRS measures the participant’s average pain over the previous seven days on a 0–10 scale where 0 is “no pain” and 10 is “worst ever pain”. This scale is easy to administer and is widely used in both research and clinical practice settings where it has been shown to demonstrate good construct validity and is sensitive to change [44].

**·****Pain Bothersomeness:** Following recommendations from a recent Cochrane review we will employ the “Bothersomeness Scale”, “Interference with Work Scale” and “Satisfaction with Current Symptoms Scale” from the “Core Set of Outcomes” [44].

#### Pain-related physical function

**·****Roland Morris Disability Questionnaire (RMDQ):** This questionnaire consists of 24 yes/no items regarding the impact of back pain on activities of daily living. The RMDQ is used widely in low back pain studies as a standardized measure of activity limitation and has demonstrated good validity, reliability and responsiveness [45,46].

**·****Patient Specific Functional Scale (PSFS):** This questionnaire is designed to assess the level of limitation on three patient-nominated activities they have difficulty performing because of their back pain. This questionnaire is anticipated to capture difficult activities that may not be represented on standardized tools. The PSFS has been shown to be a responsive measure for patients with back pain undergoing exercise-based physiotherapy treatments [47].

#### Well being

**·****European Quality of Life Questionnaire (EuroQol**): The EuroQol is a standardized instrument that provides a simple descriptive profile and a single weighted health index value for health status. It is applicable to a wide range of health conditions for which it has been shown to demonstrate good validity and reliability [48].

#### Secondary outcomes

**·****Health Care Climate Questionnaire**: is a six-item scale used to assess autonomy support that has demonstrated good reliability and validity [49].

**·****Treatment Self-Regulation Questionnaire:** This instrument is used to assess autonomous and controlled motivation. It has demonstrated good reliability and validity across diverse health-related behaviors [50].

**·****Perceived Competence Scale:** This four-item scale has consistently produced scores with good reliability and validity in relation to a variety of health-related behaviors, including PA [32].

**·****Fear Avoidance Beliefs Questionnaire physical activity subscale:** This is a five-item self-report questionnaire that specifically focuses on participants’ beliefs about how physical activity affects their low back pain [51].

**·****Objectively-measure physical activity:** We will measure all patients’ PA using a pedometer, which are relatively inexpensive (approximately €20) and provide basic data on daily step counts. A systematic review showed that pedometer scores correlated strongly (median r = .86) with accelerometer scores for step counts [52].

**Global Perceived Effect Scale (GPE):** The GPE is an 11-point NRS that assesses the patient’s perception of recovery. It is considered to have high face validity and is often used as the reference standard against which other subjective measures are tested when assessing their measurement properties [53].

#### Moderating variables

**·****General Causality of Orientations Scale (GCOS):** This is a 17-item scale that assesses the strength of different global motivational orientations within an individual [54]. Subscales for autonomous, controlled and impersonal personality types are included.

**·****Motivation to Participate Questionnaire:** to be completed by Physiotherapists in experimental arm [55], this questionnaire measures participants’ autonomous and controlled motivation for learning.

**·****Expectation of Treatment Scale:** A numerical rating scale designed to assess the therapist and patient’s expectation of the intervention/treatment. It has been used widely in studies of physical interventions and shown to be a potential influencing factor in treatment outcome [56].

**·****Depression Anxiety Stress Scale (DASS) Depression subscale:** The DASS includes a set of three self-report scales designed to measure symptoms of psychological distress including *depression, anxiety* and *stress,* this study will employ the seven-item depression subscale [57].
